The PSPCSA-YC (Portuguese version [44]) is a 24-item validated instrument to measure self-perceptions among children aged 4 to 7 years. This scale assesses perceived competence and social acceptance among children in 4 areas: cognitive competence, physical competence, peer acceptance, and maternal acceptance. For every item, the children are shown 2 pictures that depict opposite situations (for instance, one picture shows a child who can do a task, and the other picture shows a child who cannot do a task), together with a short description. The child chooses which picture they identify with and then indicates whether the statement is “totally true” or “quite true” for them, resulting in a 4-point scale for each item. In the original validation study, Harter and Pike [43] reported internal consistency coefficients (Cronbach α) ranging from 0.62 to 0.83 across the 4 subscales. The Portuguese adaptation reported a Cronbach α of 0.87 for the total scale and values ranging from 0.68 to 0.82 across subscales [45], while the Portuguese version used in the present study [44] further confirmed the 4-factor structure for Portuguese-speaking preschool and early school-age populations.

Health-Related Quality of Life The Child Health Utility 9D (CHU9D [46]; Portuguese version) is an HRQoL measure designed for use in children, reflecting the multifaceted nature of health in children and youth aged 7 to 17 years [47]. However, it can be used in children as young as 6 years, with interviewer assistance [48]. It has demonstrated acceptable to good psychometric properties across pediatric populations, including internal consistency, with Cronbach α ranging from 0.70 to 0.82 [49-51]. Evidence also supports its test-retest reliability, with moderate to strong stability over time [50,52]. Construct validity has been confirmed through the expected factor structure in confirmatory factor analyses and moderate to strong correlations with established pediatric HRQoL instruments, such as the PedsQL and KIDSCREEN (*r*=0.34-0.70) [50,53]. The CHU9D captures 9 dimensions: worry, sadness, pain, tiredness, annoyance, schoolwork, sleep, routine, and activities. For each dimension, a 5-level ordinal scale is used, ranging from 1 (no problems) to 5 (severe problems). Intended for use in cost-effectiveness analyses of youth-focused treatment and assistance initiatives [49], the instrument derives a single utility score of the health state experienced by the child from preference weights. CHU9D utility scores will be used to estimate quality-adjusted life years (QALYs) for children over the study period. In this study, we will use the self-report version.

#### Resource Use

Data on resources used by children and their caregivers will be collected at both time points via a resource use questionnaire (RUQ), adapted from questionnaires by Bouwmans et al [54] and Pokhilenko et al [55]. The RUQ will collect information on health care services (accident and emergency visits, outpatient visits, and inpatient stays), medication, child protection services, absenteeism and presenteeism from school, the use of support lines, absenteeism and presenteeism from both paid and unpaid work, and out-of-pocket expenses for caregivers.

### Data Analysis

Descriptive statistics will be calculated for all variables to summarize sample characteristics and study measures.

#### Matching Methods

Due to the study’s nonrandomized nature, there may be selection bias, whereby differences between groups (eg, age and health status) may influence outcomes, making it more challenging to isolate the effect of the intervention. To reduce potential selection bias, we will explore the use of propensity score methods to improve baseline comparability between the intervention and waitlist control groups. Propensity scores will be estimated using preintervention covariates selected a priori based on their relevance to group allocation and study outcomes. Covariate balance will be assessed using standardized mean differences and inspection of propensity score overlap. If adequate balance is not achieved or if matching substantially reduces the sample, regression-based analyses controlling for the same covariates will be used. Results will be interpreted in light of any remaining imbalance and potential residual bias [56].

#### Mixed-Effects Model Analysis

Data analysis will follow the intention-to-treat and per-protocol principles and the Standard Protocol Items: Recommendations for Interventional Trials (SPIRIT) statement guidelines for reporting and analyzing trials [57]. The confirmatory analysis of the primary end points (psychological adjustment, self-concept, and quality of life) will use mixed-effect regression modeling (hierarchical linear multilevel models) that accounts for the longitudinal structure and adjusts for potential confounders. The response variables will be the total scores and subscales of measures assessing conduct problems and self-concept, while the interaction terms between time and groups will represent the adjusted effects of the visual arts intervention and will be presented as the main study findings (hierarchical comparisons of treatment conditions with the control group). The models will also include a random intercept for the cluster to account for the nested structure of the data.

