**Methods:**

This study is a cluster nonrandomized controlled trial with children from socioeconomically disadvantaged neighborhoods. Children aged 6 to 12 years (n=156; intervention: n=104, 66.7%; waitlist control: n=52, 33.3%) will be recruited through schools and community projects. Allocation to the intervention or waitlist control group will be based on neighborhood or cluster membership. The intervention consists of 1-hour weekly visual arts sessions over 9 months led by a professional artist, culminating in community art exhibitions. Assessments will be conducted at baseline (T1) and postintervention assessment (T2) using validated measures: the Strengths and Difficulties Questionnaire (SDQ) for psychological adjustment, the Self-Perception Profile for Children (SPPC) for self-concept, and the Child Health Utility 9D (CHU9D) for HRQoL, as well as societal resource use and related costs. Quantitative data will be analyzed using regression models and intention-to-treat principles.

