### Participants

The target population will be children aged 6 to 12 years. To be eligible for the study, children must be enrolled in primary school and attending one of the 10 project institutions or partner schools and residing in socially deprived neighborhoods in Porto identified as being at risk of social exclusion. Children with a cognitive deficit, a neurological disorder, or a global developmental disorder will not be eligible.

On the basis of an expected medium effect size (Cohen *d*=0.5), an α error probability of .05, and 90% statistical power, using the difference of means between 2 independent samples with a 2:1 allocation ratio, we estimate that a total of 156 participants will be required to detect significant results (n=104, 66.7% in the experimental group and n=52, 33.3% in the control group). We anticipate fewer participants in the control group at the end of the study due to its higher likelihood of dropout [32]. Participants in the control group are not directly involved in the intervention, which may decrease their perceived benefit, reduce their engagement, and increase the possibility of withdrawal compared with those actively participating in the experimental intervention. However, if this occurs, the results will not necessarily be biased [33]. This consideration justifies the use of a 2:1 allocation ratio, ensuring sufficient statistical power despite the potential for unequal group retention rates. To account for an estimated 30% dropout or refusal rate, we will initially recruit approximately 223 participants.

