
This trial includes 2 assessment waves: (T1) baseline and (T2) postintervention assessment, 9 months after baseline. A participant timeline is provided in Figure 1. At baseline (T1), caregivers and children will provide sociodemographic information, details on family mental health history and relevant adverse RLE, and information on resources used by participants. Given that some children may experience difficulties with reading and interpreting questions, all children will rate their self-concept and HRQoL, ensuring uniformity in data collection across participants. Additionally, teachers or social project technicians (depending on the cluster) will report on the children’s behaviors, emotions, and relationships. Following the baseline assessments, participants will be assigned to either the control or intervention group without randomization. The nonrandomized assignment arises because the clusters, defined by schools or social projects, are fixed and cannot be restructured for randomization purposes. At postintervention assessment (T2), the same protocol as at baseline (T1) will be followed: caregivers will provide details on the family mental health history, relevant adverse RLE, and resources used by participants. Children will also rate their self-concept and HRQoL, while teachers or social project technicians will report on the children’s behaviors, emotions, and relationships.

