### The Art Intervention Community Galleries

The art intervention will consist of 2 parts. First, implementation of a 1-hour visual arts session (eg, painting, drawing, and printing techniques exercises) once a week for 9 months with the experimental group. Sessions are delivered in person, in real time, in a group format of 10 to 20 children per venue, across 10 community venues situated in socially deprived neighborhoods of Porto. The activities will be guided by a theme (emotions) by a qualified art facilitator (artist) with prior experience working with children to obtain a final individual artistic product. The session structure is adaptive: while the thematic focus and the artistic medium remain consistent, the facilitator adjusts pacing, complexity, and sequencing in response to participants’ receptivity and motor and cognitive capacities, given that children range in age. Each session typically includes (1) an introductory phase in which the facilitator introduces the theme and demonstrates a technique using materials such as paints, watercolors, pencils, canvas, paper, and accessible printmaking plates; (2) an active creation phase in which participants produce individual artwork independently within the group setting; and (3) an informal sharing phase in which children exchange ideas, difficulties, and improvements with peers. Through strategies such as repetition, observation, and imagination, the exercise promotes a spirit of inquiry and learning. Peer contact, shared learning, and a feeling of community are all made possible by the group-based approach. The facilitator will provide support, motivation, and technical training while guiding participants through the creative process and will also monitor adherence by collecting signatures to confirm attendance at the sessions. Using narrative-building and dialogue-based methods, the artist will encourage children to share their stories, experiences, and perspectives through art. Narrative-based techniques use narrative to investigate human experiences, emotions, and perspectives. By constructing tales via art, individuals may make sense of their experiences, manage complicated emotions, and get a better understanding of themselves. Dialogue-based strategies enable people to have meaningful conversations about their experiences. The intervention is guided by several interrelated principles. Self-expression is a foundational orientation, with participants afforded autonomy to represent their emotions and experiences according to their own visual preferences within a technically guided framework. Individual self-worth is promoted through the public display of artwork in community exhibitions. Emotional exploration constitutes the thematic spine of the program, providing a coherent and recurring psychological framework across all sessions. The session design also promotes present-moment engagement through attentive sensory involvement with materials, including awareness of hand movements, textures, and visual composition, as well as aesthetic appreciation of color, form, and harmony. Creativity and personal narrative are central to the activity design, and the group format fosters a sense of belonging and shared identity. The intervention is expected to promote emotional regulation through sustained engagement with emotion-focused creative tasks, self-concept through the experience of competence and the valorization of each child’s artistic production, relational security through the consistency of the same facilitator throughout the project and the stable composition of preexisting peer groups, and group cohesion and agency through collaborative sharing, peer learning, and guided autonomous creative choice-making.

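### With two waves, the cluster random intercept cancels from the time-by-group contrast, so type I error can exceed 5% wherever clusters differ in their change

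*Protocol article*

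**What the plan says.** The Abstract (Methods) makes the cluster the unit of allocation: "Allocation to the intervention or waitlist control group will be based on neighborhood or cluster membership". Procedures gives two measurement occasions: "This trial includes 2 assessment waves: (T1) baseline and (T2) postintervention assessment, 9 months after baseline". Participants refers to children "attending one of the 10 project institutions or partner schools", so there are about 10 clusters. The split of clusters between arms is not given.

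Mixed-Effects Model Analysis fixes the main finding: "the interaction terms between time and groups will represent the adjusted effects of the visual arts intervention". The model is one that "accounts for the longitudinal structure and adjusts for potential confounders". That implies a child-level effect but does not name one. Clustering is then dealt with in one sentence: "The models will also include a random intercept for the cluster to account for the nested structure of the data". No other cluster term is stated.

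**The concern.** The random intercept is put forward as the device that handles nesting, but for the contrast being tested it does not. It absorbs stable differences in level between clusters. Under cluster allocation, the precision of a difference in change depends on how much clusters vary in their change, and the stated model has no term for that.

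The protocol itself gives reasons to expect such variation:

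- **Raters.** The primary outcome is rated by cluster-specific adults: "teachers or social project technicians (depending on the cluster) will report on the children’s behaviors, emotions, and relationships". A shift in how one rater scores moves a whole cluster.
- **Delivery.** Sessions run "in a group format of 10 to 20 children per venue", and the facilitator adapts pacing and complexity to the group.
- **Curriculum.** Strengths and Limitations accepts that Expressive Arts teaching varies between schools.

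At stake are the p value and confidence interval of the headline result. If the standard error leaves out a real source of variation, a false positive is more likely than the nominal 5%.

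**Working it through.** **1. The cancellation.** For child i in cluster j at wave t, write the outcome as fixed effects + c(j) + b(i) + p(j,t) + e(i,t). Here c is the cluster intercept, b the child intercept, p a cluster-by-time deviation and e the residual. The change from T1 to T2 is

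fixed effects + [p(j,2) − p(j,1)] + [e(i,2) − e(i,1)].

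Both c and b are gone. The stated model has no p, so its standard error for the interaction is that of an unclustered t test on changes. Fitting mixed models with cluster and child intercepts to simulated two-wave data confirmed this. The interaction estimates equalled the raw differences in mean change. The standard errors matched those of the t test (0.1549 and 0.1549; 0.1417 and 0.1417), with a largest gap of 0.0002 in the fits inspected. Cancellation is exact for complete pairs and nearly so with some incomplete pairs.

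**2. Inputs.** From the protocol: 104 and 52 children, 10 clusters, two waves. Mean cluster size is m = 156/10 = 15.6. Assumed, because the protocol gives no value: a 7:3 cluster split, within-cluster pre-post correlation r = 0.6, intracluster correlation (ICC) 0.02 to 0.10, and cluster autocorrelation (CAC) 0.5 to 0.9. The protocol has no figure of its own on this point to reproduce.

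**3. Formulas (total variance 1).**
- Cluster-by-time variance: s_p = ICC × (1 − CAC)
- Residual variance: s_e = (1 − ICC) × (1 − r)
- ICC of change: k = s_p / (s_p + s_e)
- Design effect on change: DE = 1 + (m − 1) × k
- Actual two-sided error: 2 × [1 − Φ(1.96/√DE)]

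Example, ICC 0.05 and CAC 0.8: s_p = 0.05 × 0.2 = 0.010; s_e = 0.95 × 0.4 = 0.380; k = 0.010/0.390 = 0.0256; DE = 1 + 14.6 × 0.0256 = 1.37; √DE = 1.17; error = 9.4%.

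| ICC | CAC | k | DE | Error, formula | Error, simulated (20,000 runs) |
|---|---|---|---|---|---|
| 0.02 | 0.9 | 0.005 | 1.07 | 5.9% | 6.0% |
| 0.02 | 0.8 | 0.010 | 1.15 | 6.7% | 6.9% |
| 0.05 | 0.9 | 0.013 | 1.19 | 7.2% | 7.2% |
| 0.05 | 0.8 | 0.026 | 1.37 | 9.4% | 9.6% |
| 0.10 | 0.8 | 0.053 | 1.77 | 14.1% | 14.4% |
| 0.05 | 0.5 | 0.062 | 1.90 | 15.5% | 16.2% |
| 0.10 | 0.5 | 0.122 | 2.78 | 24.0% | 25.7% |

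The formula uses one average cluster size. The simulation uses the 7:3 split with 104:52 children, which puts larger clusters in the control arm. A second simulation (6,000 runs per setting) gave 9.7%, 14.8%, 17.5% and 25.6% for the last four rows, 5.8% to 8.2% for milder settings, and 5.0% with no cluster-by-time variance. In it, a cluster-level t test on mean change with 10 − 2 = 8 df held 4.4% to 5.2%.

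**4. If no child effect is fitted.** With a cluster intercept alone, the model takes the variance of a change as about 2 × (1 − 0.05) = 1.90, against a true 2 × (1 − r) × DE. At r = 0.6 and k = 0.05, DE = 1.73 and the true value is 0.8 × 1.73 = 1.38. The error is then 2 × [1 − Φ(1.96 × √(1.90/1.38))], about 2%. At k = 0.10 it is about 5%. At r = 0.3 the two figures are about 8% and 15%. The standard error is still wrong, but it can be conservative.

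**The case against.** **The inflation is conditional.** A reader might infer that type I error is inflated as a matter of fact. The document does not support that. It gives no intracluster correlation, autocorrelation or pre-post correlation, and with no cluster-by-time variance the test holds 5%. The same children stay in stable, preexisting groups, so mild values are plausible and the error may be only 6% to 8%. This stands and limits the size of the claim. It does not rescue the stated model, which is valid only if that variance is zero, and nothing in the protocol argues for zero.

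**The child effect is not named.** This also stands. A child effect is the natural reading of a model that handles the longitudinal structure and will also include a cluster intercept, but it is an inference. Without it the direction of the error can reverse.

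**Small-sample tests.** A reader might add that large-sample tests with about 10 clusters make matters worse. The protocol names no test or degrees-of-freedom method, and that choice commonly belongs to the analysis plan, so it is no fault here. The same goes for a rater-type-by-time term. The protocol also does not say that raters change between waves.

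**Could the analysis plan cure this?** Only by departing from the text. The random intercept and its purpose are stated, and a plan that follows them inherits the problem.

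**Conclusion.** The point holds in conditional form. The algebra is certain: with two waves and a child-level effect, the stated cluster term adds nothing to the standard error of the interaction. The size of the harm is not known. Under the assumptions above, a nominal 5% becomes about 5% with no cluster-by-time variance, 6% to 8% for ICC 0.02 to 0.05 with autocorrelation 0.8 to 0.9, and 10% to 26% for ICC 0.05 to 0.10 with autocorrelation 0.5 to 0.8. The protocol's own description of raters, delivery and curriculum makes some cluster-level variation in change plausible. Because this concerns the main finding of a trial with about 10 clusters and needs no new data to correct, it should be settled before confirmatory results are reported.

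**What to change.** Keep the time-by-group interaction as the estimand. Name the child random intercept, and add a cluster-by-time random effect alongside the cluster intercept. Use a small-sample degrees-of-freedom method (Kenward–Roger or Satterthwaite). State in advance that if the fit is singular, the confirmatory test is a cluster-level comparison of mean change on about 8 df. Record this as a dated amendment.

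A model of T2 on baseline with a cluster intercept is not an equivalent substitute, although the intercept does enter its treatment contrast. Allocation is nonrandom, and Matching Methods anticipates group differences, so the two models target different effects. With a stable baseline gap of 0.3 SD, r = 0.6 and no intervention effect, the change contrast averages 0.00, while the baseline-adjusted one averages 0.3 × (1 − 0.6) = 0.12 SD. It could serve only as a sensitivity analysis.

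The cost is one model term and a stated fallback. Intervals widen where clusters differ in change, power falls accordingly, and the added variance component is weakly estimated with about 10 clusters.

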#### Health Economic Evaluation

The health economic evaluation will follow the Consolidated Health Economic Evaluation Reporting Standards 2022 Statement [58]. A cost-utility analysis will be conducted using QALYs for children as the outcome (measured using CHU9D scores). CHU9D utility scores will be used to estimate QALYs for children over the study period using the area under the curve method [59]. Costs will be calculated from both the perspective of the Portuguese health care payer (Serviço Nacional de Saúde) and a broader societal perspective. The health care perspective will include health care costs accruing to the payer, whereas the broader perspective will include additional costs beyond the health care sector. The difference in QALYs between the intervention and control groups will be compared with the difference in costs and presented as an incremental cost-effectiveness ratio, expressed as the cost per QALY gained. Uncertainty around the cost and QALY estimates will be presented on a cost-effectiveness plane. Net monetary benefits at different willingness-to-pay thresholds will also be calculated. A cost-effectiveness acceptability curve will be used to illustrate decision uncertainty and depict the likelihood of the intervention being cost-effective across various thresholds [60].

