## Methods

### Design

The study design is a cluster nonrandomized controlled study with 2 arms: the intervention group, which includes neighborhoods participating in different activities, and a waitlist control group, which includes neighborhoods starting the intervention in year 2. The nonrandomized design was adopted because of ethical and structural constraints inherent to the community-based setting. Clusters were preexisting and defined by schools and community projects located in distinct neighborhoods. Because the participating institutions were already organized as groups, students or participants could not be redistributed or reorganized for randomization purposes. Individual randomization was also not feasible, as the intervention was delivered in a group format within each institution, that is, to a class or group simultaneously. Data collection ran from March 2024 to July 2025, and data cleaning and analysis started in April 2026.

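### The economic section does not say that QALYs will be adjusted for baseline CHU9D, costs for baseline costs, or that clustering will enter the uncertainty, although baseline utility carries half of each QALY in nonrandomized arms

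*Protocol article*

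**What the plan says.** All references are to the protocol article.

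- **Design and Procedures.** "The study design is a cluster nonrandomized controlled study with 2 arms", and after baseline "participants will be assigned to either the control or intervention group without randomization". On timing: "This trial includes 2 assessment waves: (T1) baseline and (T2) postintervention assessment, 9 months after baseline".
- **Health Economic Evaluation.** "CHU9D utility scores will be used to estimate QALYs for children over the study period using the area under the curve method". Then "The difference in QALYs between the intervention and control groups will be compared with the difference in costs", expressed as an ICER. On uncertainty: "Uncertainty around the cost and QALY estimates will be presented on a cost-effectiveness plane", with net monetary benefit and an acceptability curve. The section names no covariate and no way of handling clusters.
- **Matching Methods.** The article warns that "there may be selection bias, whereby differences between groups (eg, age and health status) may influence outcomes". Propensity score methods are to be explored, with covariates chosen in advance. If balance is poor or matching costs too many participants, regression on the same covariates takes over. The covariates are not listed, and neither QALYs nor costs are mentioned.
- **Mixed-Effects Model Analysis.** The models for psychological adjustment, self-concept and quality of life adjust for confounders, take the time-by-group interaction as the effect, and include a random intercept for cluster. QALYs and costs are not among their responses.

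**The concern.** With only two waves, the area under the curve gives baseline utility the same weight as final utility. In a randomized trial a baseline gap would be chance alone. Here the arms are existing neighborhoods, and the article names health status as a likely difference. A gap that exists before the first session then counts as QALYs gained or lost in the ICER.

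The clinical and economic analyses would also treat the same gap differently. A time-by-group interaction removes a stable baseline difference, whereas a between-group difference in area-under-the-curve QALYs keeps it.

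The second part concerns precision. Children in one venue share a school or project, a facilitator and a neighborhood. If the cost-effectiveness plane and acceptability curve treat them as independent, decision uncertainty looks smaller than it is. Cost-effectiveness is a stated secondary objective, and the article offers the result to decision-makers as a basis for allocating resources.

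**Working it through.** The article gives no utility SD, expected QALY gain, cost or ICER, so there is no figure of its own to reproduce. The inputs it does give are the interval of 9 months (0.75 year) and two utility measurements (Procedures), and groups of 10 to 20 children across 10 venues (the intervention section). Everything marked assumed below comes from outside the article.

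**1. Weight on baseline.** With utilities u1 and u2, QALY = 0.75 × (u1 + u2)/2 = 0.375 × (u1 + u2).

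**2. What a baseline gap contributes.** Let g be the baseline difference in mean utility between arms and p the share of it that would remain at T2 without any intervention effect. The unadjusted QALY difference contains 0.375 × (1 + p) × g.

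| Gap g (assumed) | p = 0 | p = 0.5 | p = 1 |
|---|---|---|---|
| 0.01 | 0.00375 | 0.0056 | 0.0075 |
| 0.02 | 0.0075 | 0.01125 | 0.015 |
| 0.05 | 0.019 | 0.028 | 0.0375 |

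**3. Comparison with the interaction form.** For g = 0.03 and p = 1 with no true effect, the change from T1 to T2 is equal in both arms, so the interaction is 0. The QALY difference is 0.375 × 2 × 0.03 = 0.0225.

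**4. Illustration for the ICER.** Assume a true T2 utility gain of 0.03, an incremental cost of 300 and p = 0.5. The QALY difference free of any gap is 0.375 × 0.03 = 0.01125, and the ICER is 300/0.01125 = 26,667.

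- g = +0.02: 0.01125 + 0.01125 = 0.0225, ICER 13,333.
- g = −0.01: 0.01125 − 0.0056 = 0.0056, ICER 53,333.
- g = −0.02: difference 0, ICER undefined.
- g = −0.03: the QALY difference turns negative.

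**5. What adjustment removes.** If b is the within-arm slope of u2 on u1, regression on baseline utility subtracts 0.375 × (1 + b) × g and leaves 0.375 × (p − b) × g. The term is removed entirely only when b = p. With b = 0.5 (assumed), the remainder per 0.01 of gap lies between 0.375 × (−0.5) × 0.01 = −0.0019 (p = 0) and +0.0019 (p = 1), against 0.00375 to 0.0075 unadjusted. For b and p between 0 and 1 the remainder never exceeds the unadjusted term in size.

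**6. Clustering.** Design effect = 1 + (m − 1) × ICC, with the stated group size as cluster size m and an assumed ICC of 0.01 to 0.10.

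- m = 10, ICC 0.01: 1.09, square root 1.04.
- m = 20, ICC 0.10: 2.90, square root 1.70.

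Standard errors that ignore clusters are too small by these factors. The ICER point estimate is not biased by this alone.

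**The case against.** The strongest reply is that the economic section is silent on adjustment, and silence is not a choice. A reader might infer that the plan has chosen an unadjusted comparison. The text does not support that: adjusted differences in QALYs and costs also form an ICER. Matching Methods is a general part of the data analysis, is not restricted to the clinical outcomes, and could reach QALYs and costs. Quality of life is a study outcome, so baseline CHU9D could be among the covariates. The article is also a condensed account, and a health economic analysis plan would often settle the regression form and the bootstrap.

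Much of this stands, and it limits the point to what the text fails to secure. It does not dispose of it. The propensity step is only to be explored, the regression fallback is conditional, and neither baseline CHU9D nor baseline costs is named. Balance on other covariates does not ensure balance on the variable that makes up half of the QALY. The cluster term is attached to the clinical models alone. The article does fix the QALY method and the group comparison, so a reader following it could obtain the biased result.

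A reader might also infer that the payer ICER treats the program as free, because "The health care perspective will include health care costs accruing to the payer". That does not follow. Counting the payer's own costs is a legitimate perspective, the societal perspective can hold delivery costs, and the article does not say that the health service funds the artist, materials or exhibitions. That a questionnaire on families' resource use omits delivery costs is no evidence that they will be left out.

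Finally, the sizes rest on assumed gaps, persistence and ICC. A stable neighborhood difference need not shrink in line with the correlation between a child's two scores, which is why persistence is shown over its full range.

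**Conclusion.** The point holds as a gap in specification with a known direction of harm. The half weight on baseline utility follows from the article's own method and two waves. Without adjustment, each 0.01 of baseline gap moves the QALY difference by 0.00375 to 0.0075, in whichever direction the gap runs. This can halve or double an ICER when the true gain is around 0.01 QALY, as in the illustration. The size of any actual gap cannot be known from the article.

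The clustering part concerns uncertainty only: standard errors too small by about 1.04 to 1.70 under the assumed ICC range, taking the stated group size as cluster size. Neither part shows that the investigators intend an unadjusted or unclustered analysis, and nothing here requires delivery cost in the payer base case.

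**What to change.** State in Health Economic Evaluation, or in the analysis plan before the data are analyzed, that:

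- incremental QALYs will be estimated by regression adjusted for baseline CHU9D utility, and incremental costs by regression adjusted for baseline costs, both with the same confounders as the clinical mixed models;
- the cost-effectiveness plane, net monetary benefit and acceptability curve will come from a model that includes the cluster level, such as a bivariate mixed model for costs and QALYs;
- the method will suit about 10 clusters. A two-stage cluster bootstrap should not be relied on alone, because there are few clusters to resample and the article does not give their split by arm;
- baseline CHU9D and baseline costs will be among the covariates if propensity scores are used.

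Residual imbalance should still be reported, since step 5 of the working shows that regression need not remove the whole gap.

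The cost is small. Table 1 shows that CHU9D and resource use are collected at baseline, so no new data are needed. The change takes some wording and a little more analysis work, and the uncertainty will probably be wider.
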